#### Secondary outcome variables

The two secondary outcome measures for the study will be 1) number of preventive home oral health practices taken by mothers to prevent caries in their young children, and 2) the mother’s readiness to change. The first outcome will be assessed by a questionnaire completed by the mother, or with assistance from the County Counselor [28,29]; the second outcome, readiness to change, will be assessed using a maternal-report “Readiness Ladder” modified for this study [30].

Additionally, several variables will be tested as mediators or moderators of the primary outcomes. These, also collected by the questionnaires, include prenatal depression [31], perceived stress [32,33], oral health impact [34], and dental anxiety [35]; and postpartum: dental anxiety [35], self-efficacy, oral health knowledge, fatalism [28,36], and child oral health impact [37].

### Intervention fidelity monitoring

Fidelity monitoring follows the framework developed by Belig and colleagues [38]. The approach focuses on three areas: (1) study design, (2) training interventionists, and (3) delivery, receipt and enactment of treatment skills during the intervention. We will use a modified Yale Adherence and Competence Scale (YACS) to rate adherence and competence in providing behavioral treatments for substance use disorders. YACS scales are reliable and have been shown to have construct and discriminant validity [39]. Intervention fidelity was monitored by coding 20% of the sessions. Other details of fidelity monitoring have been described elsewhere [22].

### Sample size

The sample size is 400 women with 80 to 120 women enrolled within any one county.

### Analysis

Three *a priori* group contrasts will be used to test the primary hypotheses regarding intervention effects on the use of dental services (see Table 1 for a summary of the 4 study groups):

(1) Groups 1 and 2 (MI Prenatal) versus Groups 3 and 4 (HE Prenatal) will test the hypothesis that the MI intervention results in a greater frequency of utilization of dental care by the woman during pregnancy.

(2) Groups 1 and 3 (MI Postpartum) versus Groups 2 and 4 (HE Postpartum) tests the hypothesis that the MI intervention results in a greater frequency of utilization of preventive dental care by the children during the first 18 months of life.

(3) Group 1 (MI Prenatal and Postpartum) versus Group 3 (MI Postpartum only) will test the hypothesis combination of MI delivered during pregnancy and postpartum will result in a greater frequency of preventive dental care for children during the first 18 months of life.

A significance level of 0.016 was used in the sample size and power calculations for the primary hypotheses to take into account the three comparisons to be performed. The study will also provide some evidence for the effect of MI during pregnancy, without MI postpartum, on child utilization. However, the study is not powered to demonstrate this effect, which will likely be modest in the absence of intervention postpartum.

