#### MI: postpartum

The first postpartum session occurs at 9 months postpartum and follows the same approach as the prenatal MI intervention but with a focus on the child. An Early Childhood Caries prevention menu is used information about oral hygiene and dietary practices and the age one dental visit. Mothers are asked to identify menu items that interest them and barriers to implementing these items are identified and discussed. This session is followed by one telephone call about six weeks afterwards to identify problems with the achievement of the mother’s stated goals.

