### Study schedule

Figure 1 summarizes the flow of study procedures from a participant’s perspective. The prenatal intervention in-person session was delivered at baseline when the participant was recruited, and the postpartum intervention was delivered, in person, when the participant’s child was nine months old. Counselors debriefed about the prenatal intervention when the participant’s child was three months old. The postpartum debrief was conducted at the study end visit.

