### Randomization and treatment contacts

Participants were randomly assigned to one of the four intervention groups using computer-generated permuted blocks of varying block sizes to ensure that the study groups would be proportionally balanced across study period and within each county and counselor. The randomization procedure was stratified on county and counselor. Study group proportions are listed in Table 1. We chose an unequal allocation to the four intervention groups, to end up with more participants with experience in the postpartum MI condition, in order to have adequate power to a test hypothesis about the combination of prenatal *and* postpartum MI versus postpartum-only MI. Overall, statistical power is adequate to detect MI versus HE differences in the primary outcomes. After participants gave consent and were enrolled, the County Counselor told the participant her prenatal study group assignment. The postpartum study group assignment was given at the 9-month postpartum visit.

**Table 1 T1:** Four-group design for the Baby Smiles study

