### Study outcomes

#### Primary study outcome variable

The primary outcome measures for the study will be dental utilization during the prenatal period and up to two months postpartum for the mother, and preventive dental utilization by 18 months for the child. These data are part of the Medicaid claims database and will be obtained from the Oregon Division of Medical Assistance Programs, which is the section of the Department of Health and Human Services that administers the Oregon Medicaid claims database. The data will include all claims related to dental procedures covered under the Oregon Health Plan by Current Dental Terminology (CDT) codes. For example the OHP-defined category “Preventive Dental Services” (CDT codes - 100 s, 1000 s) includes routine and problem-based dental exams, cleanings, and fluoride treatments.

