### Primary outcome analysis

The analysis strategy for the primary hypotheses will involve intent-to-treat analyses, where women and their children will be compared according to their randomly- assigned intervention group regardless of whether, or how much of the intervention they actually received. The only exception to the intent-to-treat rule is in our analysis for child utilization of preventive dental care; this will be limited to only live-born children (*e*.*g*., miscarriages and stillborn will be excluded). Information about fetal loss will be collected by telephone interviews by the counselors with the participants because information about miscarriages is not on the state official birth record.

Intervention effects will be tested using the three *a priori* group contrasts described previously. Separate logistic regression analyses will be used to test each contrast using a significance level of 0.016.

A preliminary step in the analysis will be to check if the women in the four intervention groups are comparable on baseline values of prior dental utilization and important predictors of dental utilization (*e*.*g*. Readiness Ladder status, oral health quality of life). If an imbalance is found between the groups, additional covariates will be included in the logistic regression analyses to adjust for baseline differences. The primary independent variable in the regression analyses will be an indicator variable for intervention group. In addition, indicator variables for county and counselor will be included in all regression models to account for the stratification of the randomization by county and counselor.

Descriptive summaries will be produced for all the primary outcomes (mother and child dental utilization) by intervention group averaged over the four study counties, as well as by county, to assess the similarity of the observed intervention effects across the different counties. Formal testing for differences in the intervention effect among counties is possible by testing for interactions between county and intervention group in the regression analyses described below. However, we do not expect the intervention effects to differ vastly among the counties, and the sample size has not been selected to test for such county differences.

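### Contrast 2 counts child visits from birth, although postpartum MI starts at 9 months: visits before then dilute the test without biasing it, by an amount the article does not allow one to fix

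*Protocol article*

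**What the plan says.** In the section Analysis, contrast 2 compares Groups 1 and 3 (postpartum MI) with Groups 2 and 4 (postpartum HE). The claim to be tested is worded: "the MI intervention results in a greater frequency of utilization of preventive dental care by the children during the first 18 months of life". The section Primary study outcome variable defines the child outcome as "preventive dental utilization by 18 months for the child", with an end point but no start date.

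Three places put the intervention at 9 months:
- MI: postpartum: "The first postpartum session occurs at 9 months postpartum".
- Study schedule: "the postpartum intervention was delivered, in person, when the participant’s child was nine months old".
- Randomization and treatment contacts: "The postpartum study group assignment was given at the 9-month postpartum visit".

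On the test, Primary outcome analysis says: "Separate logistic regression analyses will be used to test each contrast using a significance level of 0.016". The analysis is by randomised group in live-born children, with indicators for county and counselor. Further covariates enter only if the women's baseline characteristics are out of balance. No term concerns the child's own visits before 9 months.

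**The concern.** Up to 9 months, participants in the two arms of contrast 2 have been offered the same things and have not been told which postpartum arm they are in. A preventive visit in that period cannot be a result of postpartum MI. Yet with a yes/no outcome counted from birth, one such visit settles the child's result as a success for good. Nothing done at 9 months can change it, so the child adds to the rate in both arms and nothing to the difference.

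Contrast 2 has little room for such loss. The HE side has at most 104 children, because allocation was skewed to serve contrast 3, and the significance level is 0.016. What is at stake is a missed or understated effect on a primary hypothesis.

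The same window suits contrast 3, where the factor that differs is prenatal MI, which is delivered before the window opens.

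**Working it through.** **Inputs from the article**
- Table 1: postpartum MI 148 + 148 = 296; postpartum HE 52 + 52 = 104; total 400.
- Prenatal MI within contrast 2: 148/296 = 50% and 52/104 = 50%.
- Significance level 0.016 (Analysis, Primary outcome analysis). Sidedness is not stated.
- Intervention at 9 months, window to 18 months: 9/18 = half of the window comes first.

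**The plan's own figure.** The sample size of 400 cannot be reproduced, because the article gives no event rates, effect size or numerical power. The group sizes do add up to 400. The level 0.016 is 0.05/3 = 0.0167 cut to three decimals.

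**Assumptions**
- The test is two-sided.
- q is the share of children with a qualifying claim before 9 months. It is the same in both arms, since they are treated alike until then.
- r0 (HE) and r1 (MI) are the rates of a first preventive visit between 9 and 18 months among children not yet seen.
- For each r0, r1 is set so that contrast 2 has 80% power at q = 0. This is a reference point, not the plan's figure.

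**Formulas**
- Birth-to-18-month rates: p0 = q + (1 − q) r0 and p1 = q + (1 − q) r1.
- Risk difference: p1 − p0 = (1 − q)(r1 − r0).
- Power = Φ[(p1 − p0 − z·SE₀)/SE₁], with z = 2.409 for two-sided 0.016. SE₀ uses the pooled rate and SE₁ the separate rates.

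**Worked case: r0 = 0.30, r1 = 0.481, q = 10%**
- p0 = 0.10 + 0.90 × 0.30 = 0.370; p1 = 0.10 + 0.90 × 0.481 = 0.533.
- Difference 0.163, against 0.181 at q = 0. Odds ratio 1.94, against 2.16.
- Pooled rate (104 × 0.370 + 296 × 0.533)/400 = 0.491; SE₀ = 0.0570; SE₁ = 0.0555.
- (0.163 − 2.409 × 0.0570)/0.0555 ≈ 0.46, so power is about 68%.

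**Power of contrast 2 with the birth-to-18-month outcome**

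| r0, difference r1 − r0 | q = 0 | 2% | 5% | 10% | 20% |
|---|---|---|---|---|---|
| 20%, 16.9 points | 80% | 77% | 72% | 64% | 49% |
| 30%, 18.1 points | 80% | 78% | 74% | 68% | 56% |
| 40%, 18.4 points | 80% | 78% | 75% | 70% | 60% |

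**Same test among children not yet seen at 9 months.** The arm sizes become 104(1 − q) and 296(1 − q), and the rates are r0 and r1. At q = 10% that is 93.6 v 266.4, and power is 75% for all three control rates. At q = 2%, 5% and 20% it is about 79%, 77–78% and 68–69%. It exceeds the birth-window power at every q above zero that was tried.

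**The case against.** **The loss may be small.** The article gives no value for q. The program aims at a visit by age one, among families unlikely to have a usual source of dental care, so few visits before 9 months is plausible, though not established. At q = 2% the loss is 2 to 3 points. This stands: the size is conditional on q. On the other side, the qualifying category includes problem-based exams, so early claims cannot be assumed absent.

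**The 80% starting point is constructed.** The article says only that power is adequate for the primary outcomes. If the planners used cumulative 18-month rates, early visits are already in their figures. This stands too. A reader might infer that the trial is too small; the article does not support that.

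**The endpoint is legitimate.** A reader might conclude that the contrast 2 outcome should simply become a visit between 9 and 18 months in all children. That would score a child seen at 8 months and not again as a failure, although the stated objective was met. It also gains little or nothing if early visitors do not respond to postpartum MI. With r0 = 0.30 and q = 10%, power for that outcome is then 68% if 90% of early visitors return in both arms, 69% if half return and 71% if none do, against 68% for the birth window. This objection defeats replacing the window. It does not touch use of the early claim as a baseline factor.

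**Randomisation protects the comparison.** It does. A reader might infer that contrast 2 wrongly credits postpartum MI with early visits, or that prenatal MI contaminates it. Early visits favour neither arm except by chance, and prenatal MI makes up half of each side. Nor does the article say that prenatal MI aims at early child visits. It describes prenatal counseling as directed at the woman's own care, and the child effect in contrast 3 is hypothesised over the whole 18 months.

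**Conclusion.** The concern holds as one of dilution. The mismatch between a 9-month intervention and a window opening at birth is in the article's own text, and its direction, towards no difference, follows from the arithmetic. Type I error is unaffected.

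The size depends on q, which the documents do not give. For a post-9-month difference of 17 to 18 points with 80% power at q = 0, the loss is 2 to 3 points at q = 2%, 5 to 8 at 5%, 10 to 16 at 10% and 20 to 31 at 20%. These figures assume a two-sided test, q equal in the arms, HE rates of 20% to 40% and all 400 children analysed.

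This is a choice the article states, not a detail left to a fuller plan: both the window and the model are fixed there. It calls for an improvement to one primary analysis. It does not show a bias, an error in the sample size or a wrong endpoint.

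**What to change.** For contrast 2, include any preventive child claim before 9 months of age as a baseline factor, and keep the outcome as preventive care by 18 months.

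- **Model.** Every child with an early claim is already a success, so the coefficient of this factor in an ordinary logistic model would be infinite and those children would carry no information on the arms. In practice, fit the planned model to children with no such claim, which compares first preventive visits between 9 and 18 months.
- **Cut-off.** Use a fixed age of 9 months, not the date of the attended session, so that all randomised families are handled alike, including those who miss the visit.
- **Reporting.** Give early claims by arm. This shows q and checks that the arms were alike before the intervention. Report the full birth-to-18-month comparison alongside.
- **Contrast 3.** Leave it on birth to 18 months.
- **Timing.** Specify the change before the claims are analysed. The article speaks of obtaining them as still to come.

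The data cost is small, since the claims are already to be obtained. The price is in interpretation: the contrast 2 estimate then applies to children not already seen by 9 months, and this must be stated. Nor is the loss fully made good, because those children leave the comparison: at q = 10%, power is about 75%, not 80%.

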### Missing data

Based on efforts to reduce attrition and missing data shown to be effective in our previous intervention work [20], and employed in this study, we expect to have an 80% retention rate of participation over the course of the study period. We will have even less missing data regarding dental utilization because we are able to obtain utilization data from the Medicaid database on all subjects, except those who explicitly refuse further participation in the study. In the case of non-ignorable non-response, a method based on augmented inverse probability of censoring weighted estimating equations will be used to perform a sensitivity analysis that examines how the estimated intervention effect on the primary outcome measure changes over a range of plausible values for the non-response mechanism [40].

### Primary outcome analysis

The analysis strategy for the primary hypotheses will involve intent-to-treat analyses, where women and their children will be compared according to their randomly- assigned intervention group regardless of whether, or how much of the intervention they actually received. The only exception to the intent-to-treat rule is in our analysis for child utilization of preventive dental care; this will be limited to only live-born children (*e*.*g*., miscarriages and stillborn will be excluded). Information about fetal loss will be collected by telephone interviews by the counselors with the participants because information about miscarriages is not on the state official birth record.

Intervention effects will be tested using the three *a priori* group contrasts described previously. Separate logistic regression analyses will be used to test each contrast using a significance level of 0.016.

A preliminary step in the analysis will be to check if the women in the four intervention groups are comparable on baseline values of prior dental utilization and important predictors of dental utilization (*e*.*g*. Readiness Ladder status, oral health quality of life). If an imbalance is found between the groups, additional covariates will be included in the logistic regression analyses to adjust for baseline differences. The primary independent variable in the regression analyses will be an indicator variable for intervention group. In addition, indicator variables for county and counselor will be included in all regression models to account for the stratification of the randomization by county and counselor.

Descriptive summaries will be produced for all the primary outcomes (mother and child dental utilization) by intervention group averaged over the four study counties, as well as by county, to assess the similarity of the observed intervention effects across the different counties. Formal testing for differences in the intervention effect among counties is possible by testing for interactions between county and intervention group in the regression analyses described below. However, we do not expect the intervention effects to differ vastly among the counties, and the sample size has not been selected to test for such county differences.

The logistic regression models testing the primary hypotheses will be similar. They will differ in terms of the study groups to be compared and the corresponding dependent variable (i.e., mother’s or child’s receipt of dental services). In each model, the dependent variable is utilization of dental services and the primary independent variable is the study group. In addition, indicator variables for county and counselor will be included in the logistic regression to account for the stratified randomization by county and counselor. Additional analyses will also compare the intervention groups for other types (non-preventive) of dental care utilization.

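### Testing all three primary contrasts at a fixed 0.016 is valid, but Holm's step-down procedure at the same overall level is never less powerful and sometimes more

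*Protocol article*

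**What the plan says.** The Analysis section defines three primary contrasts: prenatal MI against prenatal HE for the mother's dental use (Groups 1 and 2 v 3 and 4), postpartum MI against postpartum HE for the child's preventive use (Groups 1 and 3 v 2 and 4), and both MI phases against postpartum MI only for the child (Group 1 v 3). On the level it states: "A significance level of 0.016 was used in the sample size and power calculations for the primary hypotheses", the reason being "to take into account the three comparisons to be performed".

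The Primary outcome analysis section carries the same level into the tests: "Intervention effects will be tested using the three *a priori* group contrasts described previously", and then "Separate logistic regression analyses will be used to test each contrast using a significance level of 0.016".

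No ordering, step-down or gatekeeping rule is given. The overall error rate and the sidedness are not stated in words. On power, the Randomization section says only: "Overall, statistical power is adequate to detect MI versus HE differences in the primary outcomes". The article gives no event rate, effect size or numerical power.

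**The concern.** The decision rule is written out in full, so this is not a detail left to an unseen analysis plan. It is a single-step rule, and a step-down rule with the same family-wise guarantee dominates it. Once one contrast has succeeded, at most two null hypotheses can still be true, and there is no need to go on paying for three. Under the stated rule, a contrast with a p-value between 0.016 and 0.025 is declared unproven even when another contrast is clearly significant. The same holds for one between 0.025 and 0.05 when both others have succeeded.

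What is at stake is the chance of confirming a second or third real effect. The trial asks both whether MI works and at which stage, so more than one success is a result it hopes for.

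**Working it through.** **Inputs.** Three contrasts and a level of 0.016 each (Analysis; Primary outcome analysis). Group sizes 148, 52, 148 and 52, total 400 (Table 1). Assumed, because the article gives neither: two-sided tests, and power of 50%, 80% or 90% per contrast at 0.016.

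**The plan's own figure.** 0.05/3 = 0.01667, and the Šidák level is 1 − 0.95^(1/3) = 0.01695. Neither is exactly 0.016; the stated level is 0.05/3 cut after three decimals, which errs on the safe side. Family-wise error is at most 3 × 0.016 = 0.048, and 1 − 0.984³ = 0.0472 if the tests are independent.

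**Holm's rule.** Order the p-values and compare them with 0.05/3 = 0.0167, 0.05/2 = 0.025 and 0.05, stopping at the first non-rejection. Any p-value at or below 0.016 passes every step, so nothing the plan rejects is lost. Family-wise error is at most 0.05 under any dependence.

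**Power, closed form for independent tests.** For a real effect let *a* be the power at 0.0167, *b* the extra power from 0.0167 to 0.025, and *c* the extra from 0.025 to 0.05. With 80% power at 0.016 the z-statistic has mean 3.2505. Power at the three thresholds is then 0.8042, 0.8435 and 0.9016, so *a* = 0.8042, *b* = 0.0394, *c* = 0.0580. For a null contrast *a₀* = 0.0167 and *b₀* = 0.0083.

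Power for one given real contrast under Holm:

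- Three effects real: a + b[1 − (1−a)²] + c[a² + 2ab] = 0.8042 + 0.0379 + 0.0412 = 0.883.
- Two real: a + b[1 − (1−a)(1−a₀)] + c[a·a₀ + a·b₀ + b·a₀] = 0.8042 + 0.0318 + 0.0012 = 0.837.
- One real: a + b[1 − (1−a₀)²] + c[a₀² + 2a₀b₀] = 0.8042 + 0.0013 + 0.0000 = 0.805.

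Chance of proving all three when all are real: fixed 0.016 gives 0.8³ = 0.512. Holm gives a³ + 3a²b + 3a²c + 3ab² + 6abc = 0.520 + 0.076 + 0.113 + 0.004 + 0.011 = 0.724.

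The same formulas at the other assumed powers:

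| Power at fixed 0.016 | Holm, 3 real | Holm, 2 real | Holm, 1 real | All three proven, fixed → Holm (3 real) | At least one proven, fixed → Holm (3 real) |
|---|---|---|---|---|---|
| 50% | 58.6% | 53.9% | 50.8% | 12.5% → 28.3% | 87.5% → 87.9% |
| 80% | 88.3% | 83.7% | 80.5% | 51.2% → 72.4% | 99.2% → 99.3% |
| 90% | 95.3% | 92.5% | 90.3% | 72.9% → 87.7% | 99.9% → 99.9% |

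**Checks by simulation.** Two million replicates agree with these values. Contrasts 2 and 3 are uncorrelated because Groups 1 and 3 are equal in size. A correlation of 0.3 between contrasts 1 and 3 (mother and child outcomes) changes little: at 80% power, per-contrast power is about 88% and all three rises from 53% to 73%. Holm's simulated family-wise error was at most 0.049 in every null configuration tried. Run at 0.048, so that its first step is exactly 0.016, Holm still gives 88.0% per contrast and 72% for all three. The gain therefore comes from stepping down, not from undoing the truncation.

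**The case against.** The strongest reply is that nothing here is wrong. Design and analysis use the same 0.016, error is controlled, and the trial was sized at that level. That stands: this is an efficiency point, and a reader should not infer that the stated rule is invalid or inconsistent.

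A reader might also infer that the trial is underpowered because two contrasts are small (296 v 104, equivalent to 4 × 296 × 104/400 = 308 women equally split, and 148 v 148). The article does not support this. Without event rates or effect sizes, contrast size says nothing about adequacy, and Holm's gain depends on power and on the number of real effects, not on size as such.

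It is equally tempting to quote the rise from 51% to 72% as the benefit. That is a favourable case: all three effects real, an assumed 80% power, and success on all three, which the plan does not require.

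Nor is the gain literally free. A single true null becomes easier to reject when the others are real: with two real effects at 80% power, its rejection rate rises from 1.6% to about 4.2%, within the 5% bound. The verdict on the mother's outcome would also depend on the child p-values. The present rule has simple matching 98.4% intervals, whereas unadjusted 95% intervals can contradict Holm: with p = 0.03 on one contrast and the other two non-significant, Holm does not reject, yet the 95% interval excludes no effect.

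Finally, recruitment ended in August 2011, so this would relax a published threshold after enrolment. That calls for a documented amendment but does not bar the change, since the Study outcomes section speaks of the claims data as still to be obtained.

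**Conclusion.** The point holds as one of efficiency. The fixed 0.016 rule is valid, with family-wise error of at most 0.048, but Holm at 0.05 never rejects less and sometimes rejects more, with no change to the 400 women.

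On the assumed range of power, the gain per contrast is about 5 to 9 points if all three effects are real, 2 to 4 points if two are, and under one point if one is. The chance of at least one success is essentially unchanged. These sizes rest on two-sided testing, an inferred 5% family-wise level, equal power across contrasts and near-independence. That Holm dominates the fixed rule needs only the inferred 5% level; at 0.048 it holds without that inference.

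**What to change.** By a documented amendment made before any claims outcome is seen:

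- State that the three primary contrasts are tested by Holm's procedure at family-wise 0.05: ordered p-values against 0.0167, 0.025 and 0.05, stopping at the first non-rejection. State the sidedness at the same time.
- Keep the sample-size calculation at 0.016 as the conservative case.
- Report 98.3% Bonferroni intervals (1 − 0.05/3 = 0.983), or 95% intervals labelled as unadjusted and not used for the decision.

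The cost is a short amendment with a dated record that outcomes were still unseen. No participants, data or error control are given up. The lasting downside is small: simple intervals will not always match the Holm decisions, and the text should say so.

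### Predictive baseline covariates enter the primary models only if a chance imbalance is found, so the model is not fixed in advance and some power is lost

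*Protocol article*

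**What the plan says.** All references are to the protocol article, section Primary outcome analysis, unless another section is named.

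- The primary tests: "Separate logistic regression analyses will be used to test each contrast using a significance level of 0.016".
- Covariates that are always present: "indicator variables for county and counselor will be included in all regression models". These are the stratification factors, and no other covariate is fixed in advance.
- Before the models are run, the plan checks whether the women in the four groups are "comparable on baseline values of prior dental utilization and important predictors of dental utilization". Readiness Ladder status and oral health quality of life are given as examples.
- What follows from the check: "If an imbalance is found between the groups, additional covariates will be included in the logistic regression analyses to adjust for baseline differences".

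No other section commits to using these variables whatever their balance.

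**The concern.** Assignment was by stratified permuted blocks (Randomization and treatment contacts), so a baseline difference between groups is a chance event. What makes a covariate worth including is how well it predicts the outcome, and observed balance says nothing about that. The plan already regards these variables as predictive, yet leaves them out whenever they happen to balance.

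Two things are at stake.

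1. **The confirmatory model.** Its covariates are settled only after baseline data have been compared by group. In logistic regression the odds ratio with a predictive covariate in the model is a different quantity from the one without it, so chance also decides which odds ratio is reported.
2. **Power.** Leaving predictive covariates out of a logistic model costs power, and under this rule they are left out most of the time.

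**Working it through.** **Inputs from the article.** Table 1 gives groups of 148, 52, 148 and 52, and 148 + 52 + 148 + 52 = 400, which matches the stated sample size. The contrasts in the Analysis section are therefore:

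- contrast 1: 148 + 52 = 200 v 200
- contrast 2: 148 + 148 = 296 v 52 + 52 = 104
- contrast 3: 148 v 148

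Each is tested at 0.016 (3 × 0.016 = 0.048). Power is called adequate but no figure is given, and neither event rates nor effect sizes are stated. There is thus no power figure to reproduce, and everything below rests on stated assumptions.

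**How often the trigger fires.** Assume imbalance means p < 0.05 in a baseline comparison of the two sides of a contrast. With k independent covariates, the chance that at least one is flagged is 1 − 0.95^k:

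- k = 3: 1 − 0.95³ = 0.143
- k = 5: 1 − 0.95⁵ = 0.226

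With three covariates, about 86% of trials would run the primary model without any of them.

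**Power, first set of assumptions.** 3,000 simulated trials per cell; two-sided 0.016; five county/counselor strata in every model; three independent normal covariates; conditional treatment log-odds ratio 0.7; event rate about 50%. Covariate log-odds ratios per SD were 0.3/0.2/0.2 (weak), 0.6/0.4/0.3 (moderate) or 1.0/0.5/0.4 (very strong; e^1.0 = 2.72 per SD for the largest).

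| Contrast | Predictors | Trigger rule | Always adjust | Gain (points) |
|---|---|---|---|---|
| 1 | weak | 82.5% | 84.1% | 1.6 |
| 1 | moderate | 74.8% | 79.9% | 5.1 |
| 1 | very strong | 63.3% | 75.5% | 12.2 |
| 2 | weak | 69.4% | 71.1% | 1.7 |
| 2 | moderate | 61.2% | 67.3% | 6.1 |
| 2 | very strong | 48.7% | 60.4% | 11.7 |
| 3 | weak | 70.1% | 72.0% | 1.9 |
| 3 | moderate | 60.4% | 66.9% | 6.5 |
| 3 | very strong | 49.3% | 59.9% | 10.6 |

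The trigger rule performs almost like never adjusting. For contrast 1 with very strong predictors, power without adjustment was 62.1%, against 63.3% under the rule.

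**Power, second set of assumptions.** Contrast 1 only, conditional treatment log-odds ratio 0.75, two covariates: prior dental use (yes/no) and readiness (per SD).

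| Odds ratios, prior use / readiness | Trigger rule | Always adjust | Gain (points) |
|---|---|---|---|
| 1.5 / 1.2 | 88.8% | 88.9% | 0.1 |
| 2 / 1.3 | 87.4% | 88.1% | 0.7 |
| 3 / 1.5 | 82.9% | 86.3% | 3.4 |
| 4 / 1.7 | 76.6% | 83.0% | 6.4 |

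**Type I error.** With no treatment effect, in the first set, rejection rates were 0.011 to 0.017 under the trigger rule and 0.012 to 0.019 with prespecified adjustment. The Monte Carlo standard error is √(0.016 × 0.984 / 3000) = 0.0023, so neither departs from 0.016 by more than simulation noise would explain.

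**Which odds ratio.** For contrast 1 with very strong predictors, the mean treatment log-odds ratio was 0.558 without adjustment, 0.565 under the trigger rule and 0.722 with full adjustment. The result under the rule is a mixture of two quantities, weighted by how often imbalance happens to occur.

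**The case against.** **Details may sit elsewhere.** A full analysis plan, not shown, would normally hold the imbalance threshold and the exact covariate list. That stands, and their absence is not the complaint. The conditional rule itself is stated in the article, and nothing else there offsets it. The model is also not wholly open: county and counselor are always included and the domains to be checked are named.

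**The size depends on inputs the article does not give.** This also stands. With weak predictors the loss is negligible, and the largest figures need very strong ones. Only a range can be reported.

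**Stronger readings that the documents do not support.**

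- A reader might infer that choosing covariates from the data inflates the false-positive rate. The simulations of a mechanical trigger show no such inflation.
- A reader might take the smaller unadjusted log-odds ratio as bias. It is non-collapsibility: a valid estimate of a different, marginal odds ratio.
- A reader might think contrast 2 is confounded because its model omits the prenatal assignment. Table 1 rules this out: the prenatal MI share is 148/296 = 50% in the postpartum MI arm and 52/104 = 50% in the postpartum HE arm. Adding the term raised simulated power by about 0.3 to 1.4 points for prenatal log-odds ratios of 0.3 to 0.7. It is an optional gain in precision.
- A reader might call the power gain free. It needs no extra participants, but it makes the target a covariate-conditional odds ratio and requires a rule for missing baseline answers.

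**Conclusion.** The point holds as a weakness in a stated rule. It does not invalidate the trial. Entry of predictive covariates into the three primary models depends on chance imbalance, so neither the model nor the odds ratio it estimates is fixed in advance. Variables that the plan regards as predictive are usually left out: in about 86% of trials if three independent covariates are screened at 0.05.

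The power loss relative to prespecified adjustment is from under 1 to about 2 points for weak predictors, about 3 to 6 for moderate ones and about 11 to 12 for very strong ones. These figures rest on assumed event rates, treatment effects, covariate effects and a 0.05 imbalance threshold, none of which the article supplies. Confidence is high about the rule and only moderate about its size in this trial.

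**What to change.** Delete the imbalance trigger. State that all three primary logistic models include prior dental utilization, baseline Readiness Ladder status and oral health quality of life, alongside the county and counselor indicators, whatever the observed balance. Keep the baseline comparison as description only. Report the model without these covariates as a sensitivity analysis.

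Two sentences should go with it: one saying that the reported odds ratio is conditional on the covariates, and one giving a rule for missing baseline questionnaire values, such as a missing indicator or single imputation. Prenatal assignment may be added to the contrast 2 model if wanted.

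The cost is about one paragraph. The plan already intends to examine these variables at baseline, and a questionnaire was given at enrollment. The article does not say where prior utilization comes from, so its source should be confirmed. The Medicaid claims are described as still to be obtained, so the covariates should be fixed before those data are seen.
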